### Recruitment

When the psychiatrist or clinical psychologist identifies a potential participant, he or she will describe the study characteristics to him/her. Those candidates interested in participating will sign an informed consent, and the professional will fill out a document describing the participant’s sociodemographic and clinical characteristics, and give him/her a patient information sheet and a handout describing the study. After confirming that the participant has signed the informed consent and understands the study and the treatment options, the researcher will administer assessment instruments related to the inclusion criteria. If the patient fulfills all the study criteria, the researcher will contact an independent researcher to implement randomization. Participants who meet all the inclusion criteria will then be randomized to either EmotionRegulation or TAU and complete the remaining assessment instruments. Participants will be free at any time to withdraw from the treatment or the study without giving any explanation.

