**Methods/Design:**

The study is a randomized controlled trial. 200 participants recruited in specialized care will be allocated to one of two treatment conditions: a) EmotionRegulation or b) treatment as usual. Primary outcome measures will be the BAI and the BDI-II. Secondary outcomes will include a specific measure of the principal disorder, and measures of neuroticism/behavioral inhibition and extraversion/behavioral activation. Patients will be assessed at baseline, post-treatment, and 3- and 12-month follow-ups. Intention to treat and per protocol analyses will be performed.

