### Eligibility criteria

Inclusion criteria will include the following: a) be 18 years or older; b) ability to understand and read Spanish; c) access to Internet at home and having an email address; d) meeting the DSM-IV diagnostic criteria [78] for ED (MDD, DD, MDNOS, PD, A, SAD, GAD, ADNOS, OCD); and e) providing written, informed consent. Exclusion criteria include the following: a) suffering from a severe mental disorder (schizophrenia, bipolar disorder, and alcohol and/or substance dependence disorder); b) the presence of a high risk of suicide; c) medical disease/condition that prevents the participant from carrying out the psychological treatment; or d) receiving another psychological treatment during the study in the experimental group. Receiving pharmacological treatment is not an exclusion criterion during the study period, but patients having an increase and/or change in the medication 2 months prior to enrollment will not be considered for the trial. Also, the increase and/or change in the medication during the study period in the experimental group will imply the participant’s exclusion from subsequent analyses (a decrease in pharmacological treatment is accepted).

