### Randomization and blinding

Patients will be randomly allocated in a 1:1 ratio to either of the two groups (EmotionRegulation or TAU) using a computer-generated random number sequence. The Epidat 4.1 program will be used to generate this sequence. The allocation will be carried out by an independent researcher who will be unaware of the characteristics of the study. The sequence will be concealed until interventions are assigned. Patients will agree to participate before the random allocation and without knowing to which treatment they will be allocated. Study researchers conducting psychological assessments (that is, diagnostic interviews) throughout the entire study will be masked to the participants' treatment conditions and unaware of the treatment group to which the patient belongs. For ethical and practical reasons, participants will not be blind to the treatment conditions.

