### Support

Meta-analyses have shown that attrition rates are higher when no support of any kind is provided to patients in self-administered Internet-based programs [60, 68]. Therefore, we will provide human support and ICT support to all participants in EmotionRegulation.

Human support will be provided by trained pre-doctoral students in our group and will include the following: a) an initial face-to-face session to explain the participant the characteristics of the study and to administer the diagnostic interview to confirm him/her to fulfill the eligibility criteria, b) an initial phone call encouraging participants to start the intervention once baseline assessments have been completed, and c) one weekly brief phone call (maximum of 10 minutes) during the treatment period. The objective of these weekly phone calls will be as follows: 1) to ask the participants about any difficulties or doubts they might have found in the use of the online protocol and help them to solve those problems, 2) to remind them to review the treatment contents as many times as necessary, 3) to emphasize the importance of doing the homework tasks, 4) to encourage participants to keep using the protocol and reinforce them for engaging in the treatment, and 5) to recommend that they complete one module per week. Finally, d) a final phone call will be made after the 18-week treatment period to remind participants that they will be allowed to use the program at any time they want during the trial period and that they will be contacted for follow-up assessments.

ICT support will consist of two weekly mobile phone text messages with reminders about the importance of doing the homework tasks and encouraging participants to review the modules. A commercial platform (www.trendoo.es) will be used to send these messages.

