#### Primary outcomes

Beck Anxiety Inventory (BAI) [81]. The BAI is a 21-item self-report measure designed to assess anxiety, with a maximum of 63 points. Each item has a four-point severity scale (for example, not at all, mildly, moderately, and severely) that addresses symptoms experienced during the past week. The internal consistency of the BAI has been found to range from .85 to .94, and it has shown adequate convergent and divergent validity. The Spanish version of the BAI has shown high internal consistency (α = .93) [82].

Beck Depression Inventory (BDI-II) [83]. It is one of the most widely used questionnaires to evaluate depression severity in pharmacological and psychotherapy trials. It consists of 21 items about the different symptoms characterizing major depression disorder, added together to obtain the total score, which can be a maximum of 63 points. The instrument has good internal consistency (α = 0.76 to 0.95). The Spanish version of this instrument has also shown a high internal consistency (α = 0.87) for both the general and clinical populations (α = .89) [84].

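### The stated order puts randomisation before the remaining instruments, which appear to include the baseline BAI and BDI-II, so unblinded participants may know their arm when they give baseline scores

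*Protocol article*

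**What the plan says.** The Recruitment section gives the order of steps. After consent, "the researcher will administer assessment instruments related to the inclusion criteria". If the patient qualifies, the independent researcher is contacted for randomisation. Then: "Participants who meet all the inclusion criteria will then be randomized to either EmotionRegulation or TAU and complete the remaining assessment instruments".

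Other sections bear on what the remaining instruments are and what participants know when they complete them:

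- **Eligibility criteria** requires "meeting the DSM-IV diagnostic criteria" for one of the listed emotional disorders. It sets no score on either Beck scale.
- **Support** describes an initial face-to-face session, one purpose of which is "to administer the diagnostic interview to confirm him/her to fulfill the eligibility criteria". It also describes "an initial phone call encouraging participants to start the intervention once baseline assessments have been completed".
- **Abstract, Methods/Design**: "Primary outcome measures will be the BAI and the BDI-II". Table 3 schedules both at baseline.
- **Primary outcomes**: "The BAI is a 21-item self-report measure designed to assess anxiety". The BDI-II is described as a questionnaire.
- **Randomization and blinding**: "participants will not be blind to the treatment conditions". Masking covers the researchers who conduct the diagnostic interviews, and concealment of the sequence ends at assignment.

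**The concern.** A baseline is useful because allocation cannot have influenced it. If a participant rates anxiety and depression after learning whether they will receive the new programme or continue usual care, hope or disappointment can enter the score. The measure then ceases to be a pre-randomisation variable, although it is still labelled baseline.

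Four uses of it are exposed. The Analysis section plans tests that the arms are comparable at baseline; these could not separate chance imbalance from a reaction to allocation. It plans standardised within-group effect sizes, which would absorb each arm's own reaction. Any between-arm contrast of change would carry the difference in reaction. Any baseline-adjusted contrast would carry part of it. In addition, a participant unhappy with the allocation may withdraw before giving a baseline, and this may happen more often in one arm.

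**Working it through.** **Step 1: which instruments follow randomisation.** The plan states no figure on this point, so the check sets the sections side by side.

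1. Before randomisation come only the instruments that bear on inclusion (Recruitment).
2. Inclusion rests on a diagnosis, with no BAI or BDI-II cut-off (Eligibility criteria), and the diagnostic interview confirms eligibility (Support).
3. BAI and BDI-II are baseline measures (Table 3) and must be collected at some point.
4. They therefore fall among the remaining instruments. This is a deduction, since Recruitment does not list those instruments.

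Table 2 points the same way. The pre-treatment instruments can be completed online in the programme, and during the study the programme is open only to the EmotionRegulation arm. A pre-assessment taken there would follow allocation.

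**Step 2: what protects the baseline.** Agreement to take part precedes allocation, which protects enrolment. Masking of interviewers does not reach self-report scales. The first support call follows completion of baseline, so baseline precedes encouragement to start the programme. No visible section places the questionnaires before allocation or its disclosure.

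**Step 3: illustrative size.** Assumptions, none of them in the documents:

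- b is the difference between arms in the baseline shift caused by knowing the allocation, in SD units. An equal shift in both arms gives b = 0.
- r is the correlation between baseline and post-treatment scores.
- The SD is the same at both times, and post-treatment scores are unaffected by the shift.

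Formulas: bias in a change-score contrast = b; bias in a baseline-adjusted contrast ≈ r × b. Each is compared with the planned d = 0.40 (Sample size).

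| b | Change score | Adjusted, r = 0.3 | Adjusted, r = 0.5 | Adjusted, r = 0.7 |
|---|---|---|---|---|
| 0.10 | 0.10 (25%) | 0.03 (7.5%) | 0.05 (12.5%) | 0.07 (17.5%) |
| 0.20 | 0.20 (50%) | 0.06 (15%) | 0.10 (25%) | 0.14 (35%) |

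For example, 0.10/0.40 = 25%, and 0.5 × 0.20 = 0.10, with 0.10/0.40 = 25%.

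**Step 4: direction.** Higher scores mean worse symptoms. Disappointment in TAU would raise its baseline, and hope in EmotionRegulation would lower its baseline. Either leaves TAU more apparent room to improve and EmotionRegulation less. A true 0.40 would then appear in change scores as 0.40 − 0.10 = 0.30 or 0.40 − 0.20 = 0.20. A reaction of the opposite sign would overstate the benefit by the same amounts.

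**The case against.** The strongest reply is that two links are inferred. Recruitment does not list the remaining instruments, and the suicide-risk exclusion names no instrument, so a questionnaire with such items could in principle have been given earlier. Nor does any section say when the participant learns the allocation. Fig. 1 is not shown and may settle the order. This stands as a limit on certainty, but the wording prescribes randomisation first and describes no safeguard.

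A reader might go further and infer any of the following. The documents do not support them.

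- **That participants do know their arm when they complete baseline.** The text shows only that they are unblinded and that the order permits it.
- **That the bias has a known size, or favours the new programme.** The shift and r are assumed. The most natural reactions would understate benefit in change scores.
- **That every planned estimate is biased.** The Analysis section names mixed models with full information maximum likelihood but not how baseline enters them. A post-treatment comparison that ignores baseline would not carry this bias.
- **That participants without a baseline are lost.** Intention-to-treat with full information maximum likelihood can retain someone who has later data, if baseline is modelled as an outcome. Differential loss is a risk, chiefly from those who give no data at all.

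The support call that follows baseline says nothing about allocation. It does suggest that any contamination would come from knowing the arm and not from exposure to treatment.

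**Conclusion.** The point holds as a weakness in the prescribed order. On the text, the baseline BAI and BDI-II appear to be completed after randomisation by participants who are not blind, with nothing to ensure that this happens before they learn their arm. Baseline can therefore react to allocation, and some randomised participants may have no baseline.

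The size and direction are unknown. Under an assumed shift of 0.10 to 0.20 SD, a change-score contrast is off by the full shift (25% to 50% of d = 0.40). A baseline-adjusted contrast is off by about 0.03 to 0.14 SD for r between 0.3 and 0.7. These figures show scale only; the case rests on the order of steps. The conclusion would fall away if Fig. 1 or site practice placed the questionnaires before disclosure, in which case the Recruitment section should say so.

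**What to change.** Amend Recruitment so that, once eligibility is confirmed, all baseline questionnaires are completed and locked before the independent randomiser is contacted, or at minimum before allocation is disclosed. Name the instruments and state when disclosure occurs. Use a collection route open to both arms, since the programme itself opens only to the EmotionRegulation arm. The treatment expectation scale is a separate case: it follows the welcome module by design and should not be treated as a pre-randomisation measure.

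For participants already enrolled, record the dates of baseline, allocation and disclosure. Add a sensitivity analysis that compares post-treatment BAI and BDI-II by randomised arm without using the post-allocation baseline. Restricting an analysis to baselines taken before allocation would not help for this group: if the stated order was followed, it would contain nobody.

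The cost is small, and Trial status says recruitment is still open. No measure is added, but a common collection route may have to be set up. A few patients may complete questionnaires and not be randomised. Baseline timing will differ between earlier and later enrollees and should be reported.

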### Randomization and blinding

Patients will be randomly allocated in a 1:1 ratio to either of the two groups (EmotionRegulation or TAU) using a computer-generated random number sequence. The Epidat 4.1 program will be used to generate this sequence. The allocation will be carried out by an independent researcher who will be unaware of the characteristics of the study. The sequence will be concealed until interventions are assigned. Patients will agree to participate before the random allocation and without knowing to which treatment they will be allocated. Study researchers conducting psychological assessments (that is, diagnostic interviews) throughout the entire study will be masked to the participants' treatment conditions and unaware of the treatment group to which the patient belongs. For ethical and practical reasons, participants will not be blind to the treatment conditions.

### Interventions

#### Transdiagnostic Internet-based protocol (EmotionRegulation)

Our research group developed a transdiagnostic protocol made up of 12 modules designed for the treatment of the following mental disorders: MDD, DD, MDNOS, PD, A, SAD, GAD, ADNOS and OCD. This protocol is partly based on the UP by David H. Barlow [37] and partly on the emotion regulation skills from DBT by Marsha Linehan [52]. The intervention aims to enhance present-focused emotional awareness, facilitate cognitive flexibility, identify and modify behavioral and emotional avoidance patterns, and promote interoceptive and situational exposure. Each module includes several tasks to practice the different techniques and skills.

We have adapted this protocol for its application on the Internet (EmotionRegulation). EmotionRegulation is an internet-delivered, multimedia, interactive, self-administered program for ED that allows the individuals to learn and practice adaptive ways to regulate their emotions from a transdiagnostic perspective. EmotionRegulation will be delivered through a web platform (https://www.psicologiaytecnologia.com/) designed by our research group. This web platform has four main sections (shown in Table 1).

**Table 1 Tab1:** Main sections of the web platform (https://www.psicologiaytecnologia.com/)

a) “Home”: This section is the start point from which participants can access the other sections. It also displays a progress bar (0 to 100 %) that shows the progress through the treatment.	
b) “Calendar”: This section shows pending tasks as well as the days in which the participant has accessed the program and has done the module tasks.	
c) “Review”: This section allows participants to review the treatment modules already done as many times as they want.	
d) “How am I?”: This section allows participants to monitor their progress through several graphs as they advance in the program.	

EmotionRegulation includes a Welcome module that provides the participant with general information about the protocol and its objectives, as well as recommendations for benefiting from it, and the following 12 treatment modules:M1. Emotional disorders and emotion regulation. This module provides information about the role of emotion regulation in emotional disorders. A brief description of the program modules is also presented, as well as videos with examples of people suffering from different ED.M2. Motivation for change. The aims are to analyze the advantages and disadvantages of changing, emphasize the importance of being motivated, and highlight the importance of establishing significant life goals.M3. Understanding the role of emotions. This module provides information about the adaptive roles and functions of emotions and the three-component model of emotions.M4. The acceptance of emotional experiences. This module aims to teach the patient the acceptance of emotional experiences and its importance in the treatment.M5. Practicing acceptance. The objective is to continue to learn about the acceptance of emotional experiences and increase awareness of physical sensations, thoughts, emotions and daily activities.M6. Learning to be flexible. It focuses on the importance of maladaptive ways of thinking in the maintenance of emotional disorders, and on learning how to identify them.M7. Practicing cognitive flexibility. This module aims to teach the patients the ways maladaptive ways of thinking can be modified. It also provides information about intrusive thoughts and how to deal with them.M8. Emotional avoidance. This module aims to teach the patients the emotion avoidance strategies that contribute to the maintenance of emotional disorders.M9. Emotion Driven Behaviors (EDBs). The aim is to learn the concept of EDBs, and replace their own maladaptive EDBs with other more adaptive behaviors.M10. Accepting and facing physical sensations. The objectives are to teach the patients the role of physical sensations in the emotional response and train them in interoceptive exposure, in order to increase tolerance and promote habituation to physical sensations.M11. Facing emotions in the contexts in which they occur. The purpose is the construction of exposure hierarchies to help the patients to begin to face the avoided situations that contribute to the maintenance of the problem.M12. Relapse prevention. This module aims to review the strategies learned throughout the program and teach the patient how to identify and cope with future high-risk situations.

These modules are sequential, in order to move through the program step by step. The program duration can vary among the users, and it is estimated that for most participants the duration will be 18 weeks. During the study, EmotionRegulation will be accessible only to participants in the online intervention group. Participants will be allowed to use the program at any time they want during the trial period. See Table 2 for other functionalities in EmotionRegulation.

**Table 2 Tab2:** Other functionalities in EmotionRegulation

a) Assessments: The program allows the pre-, post- and follow-up instruments to be completed online.	
b) Module self-assessments: Each module ends with a short list of multiple-choice questions that allow participants to assess their understanding of the module and help them to decide whether they need to review its contents.	
c) Automatic e-mails with reminders when participants have not accessed the program in the past 15 days.	
d) Suicide risk alarms: Therapists receive warnings of participants with high risk of suicide (when participants answer questionnaires that include items assessing high suicide risk)	
e) Post-module questionnaires: Each module includes three brief questionnaires (OASIS, ODSIS and PANAS) to evaluate anxiety, depression and positive/negative affect after each treatment module. Participants are able to monitor these scores in the feedback section through the ‘How am I?’ button.	
f) Printable documents: Each module contains several printable documents (PDF) with summaries and self-monitoring sheets that participants are encouraged to use to practice the skills and strategies.	

Participants in the EmotionRegulation condition will be allowed to maintain medication if there are not changes and/or increases but will not be allowed to receive another psychological treatment during the study period. Failure to fulfill these criteria will result in the participant’s data being excluded from data analysis.

#### Treatment as usual

Treatment as usual (TAU) is treatment as delivered in current daily practice by psychiatrists and clinical psychologists in the mental health centers in Spain. TAU may refer to psychiatric treatment, which typically includes prescription and monitoring of antidepressant and/or anxiolytic medication, psychological treatment (this may include case management, group psychotherapy, empathic listening and/or supportive counselling), or a combination of both. Patients in the TAU condition already receiving any of the aforementioned treatments are informed they will continue to receive as usual the services received before enrollment in the study.

### Support

Meta-analyses have shown that attrition rates are higher when no support of any kind is provided to patients in self-administered Internet-based programs [60, 68]. Therefore, we will provide human support and ICT support to all participants in EmotionRegulation.

Human support will be provided by trained pre-doctoral students in our group and will include the following: a) an initial face-to-face session to explain the participant the characteristics of the study and to administer the diagnostic interview to confirm him/her to fulfill the eligibility criteria, b) an initial phone call encouraging participants to start the intervention once baseline assessments have been completed, and c) one weekly brief phone call (maximum of 10 minutes) during the treatment period. The objective of these weekly phone calls will be as follows: 1) to ask the participants about any difficulties or doubts they might have found in the use of the online protocol and help them to solve those problems, 2) to remind them to review the treatment contents as many times as necessary, 3) to emphasize the importance of doing the homework tasks, 4) to encourage participants to keep using the protocol and reinforce them for engaging in the treatment, and 5) to recommend that they complete one module per week. Finally, d) a final phone call will be made after the 18-week treatment period to remind participants that they will be allowed to use the program at any time they want during the trial period and that they will be contacted for follow-up assessments.

ICT support will consist of two weekly mobile phone text messages with reminders about the importance of doing the homework tasks and encouraging participants to review the modules. A commercial platform (www.trendoo.es) will be used to send these messages.

